**Methods/Design:**

Women who are clinically diagnosed as unilateral BCRL, with a 10% to 40% increase in volume compared to the unaffected arm, will be recruited. Following baseline assessment, participants will be randomized to either the real acupuncture group or sham-acupuncture group at a ratio of 1:1, and given a standard real acupuncture or sham-acupuncture treatment accordingly on both arms followed by the same usual care of decongestive therapy. Volume measurements of both arms will be performed for every participant after each treatment. Data collected at baseline and the last session will be used to calculate the primary outcome and secondary outcomes. Other data will be exploited for interim analyses and trial monitoring. The primary outcome is the absolute reduced limb volume ratio. Secondary outcomes are incidence of adverse events and change in quality of life. A t test or non-parameter test will be used to compare the difference between two groups, and assess the overall effectiveness of acupuncture using the SPSS software (version 12).

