### Data collection

Before the first treatment session, every participant will get an assessment of both limbs by perometer, which is an automated infrared light digital scanner equipped with a microcomputer. When the limb is placed inside, the infrared light transmitters located on two sides of the perometer will be activated, and the blockage of the transmission of infrared light from both sides caused by the limb will be recorded and calculated. As the transmitters move along the limb, a series of images will be recorded. Hence a highly accurate measurement of the limb size and volume will be created. And these results will serve as the baseline data. Following the treatment of each session, participants in both groups will be asked to take assessments to get the interim data. Upon the last session, the assessments of both limbs will be adopted as the end-point data. For each arm, the measurement will repeat 3 times to ensure the reliability. Table 1 illustrates all the time points when measurements are taken during the whole procedure.

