### Sample size calculation

As no two-arm, randomized, multi-centered, sham-controlled trial has been performed on this topic, no existing data regarding the sample size are available. However, based on our preliminary clinical data collected and a similar study [41], we assume that the mean and SD of ARLVR in the real-acupuncture group and sham-acupuncture group are (0.32, 0.25) and (0.22, 0.2), respectively, and after calculation using G-Power (V.3.1), the effect size (ES) is 0.4417261. Next we input the parameters above, set the alpha risk (α, type 1 error risk) and beta risk (β, type II error risk) at 0.05 and 0.2 respectively, and choose “t test from two independent groups” and “A Priori: Compute required sample size given α, power and effect size”, then after calculating, the required sample size is 164 (Additional file 2). Assuming the loss to follow-up rate is 20%, then 197 is the total minimum sample size required in this trial. However, to increase the power and make full preparation, we decided to recruit 200 participants, 100 for each arm in this trial.

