### Statistical and data analysis

Upon the receipt of the final data, the Kolmogorov-Smirnov test (K-S test) will be performed, followed by a test for homogeneity of variance to see whether the variances are equal between groups. If the data distribution fits a normal distribution with equal variance, the independent t test will be employed; otherwise, nonparametric test will be chosen to determine whether there is significant difference between the real acupuncture group and the sham acupuncture group. Moreover, one-way ANOVA will be performed to see whether there is significant difference between three centers. Analysis of covariance adjusted for clinical center and baseline will be applied on the condition that significant difference exists between three centers. In addition, regression analysis will be performed to analyze the effects of co-variances (risk factors) such as BMI, axillary lymph node dissection, postoperative radiotherapy, infection, and history of lymphangitis on the overall outcome of this treatment. A type I level error < 0.05 will be interpreted as statistically significant and 95% CI, mean, and SD will be calculated. Data analysis in this trial will consist of an intent-to-treat (ITT) analysis, a per-protocol (PP) analysis and an interim analysis. The ITT analysis will collect data from all the participants in this trial, and for those loss to follow-up, the last observation carried forward method will be implemented. As for the PP analysis, data collection will be rigorous, and only those participants who strictly comply with the protocol are eligible. The interim analysis in this trial performed by DSMB, will use the interim data collected during the trial to actively monitor the operating status of the trial and help find problems timely. All statistical analyses will be conducted using the SPSS software (version 12).

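### LOCF is the fixed ITT rule for a last-session endpoint: if response builds over the sessions it can bias the arm difference either way, while session-by-session volumes that support a better analysis go unused

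*Protocol article*

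**What the plan says.** - **Missing-data rule.** Protocol article, Statistical and data analysis: "Data analysis in this trial will consist of an intent-to-treat (ITT) analysis, a per-protocol (PP) analysis and an interim analysis". Within the ITT analysis, "for those loss to follow-up, the last observation carried forward method will be implemented". No other missing-data method is named.
- **Endpoint.** Data collection: "Upon the last session, the assessments of both limbs will be adopted as the end-point data". The Primary outcome section likewise builds ARLVR from baseline and last-session volumes.
- **Intermediate volumes.** Data collection: "Following the treatment of each session, participants in both groups will be asked to take assessments to get the interim data". The abstract agrees: "Volume measurements of both arms will be performed for every participant after each treatment".
- **Their use.** Abstract, Methods/Design: "Data collected at baseline and the last session will be used to calculate the primary outcome and secondary outcomes". It continues: "Other data will be exploited for interim analyses and trial monitoring".
- **Expected loss.** Sample size calculation plans for 20% loss to follow-up, which is about 40 of the 200 participants to be recruited.
- **Withdrawal.** Loss to follow-up and data management foresees an evaluation when a participant withdraws, but only where feasible. It takes place at the time of leaving, not at week 4.

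**The concern.** LOCF takes a participant's value at the last measured session as the value at session 12 and analyses it as if it had been observed. If the response is still developing when the participant leaves, a partial-course value stands in for a full-course one. Each arm's mean is then pulled toward zero by an amount that depends on how many leave that arm and how early. The difference between arms can shrink or grow, so LOCF cannot be defended as conservative.

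The protocol itself gives reasons why loss might differ between arms. The Discussion accepts that some sham participants may notice the difference. Real needles penetrate the skin and the sham device does not, while Patient health monitoring links broken skin to infection, interruption of treatment and, for unfit patients, leaving the trial. These are possibilities, not predictions.

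At stake are the primary ITT estimate and its type I error. The rule is stated in the protocol, so it is not a detail left to an unseen analysis plan.

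**Working it through.** **1. The plan's own figure.** Sample size calculation gives ARLVR means (SD) of 0.32 (0.25) real and 0.22 (0.20) sham.

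- Pooled SD = √((0.25² + 0.20²)/2) = 0.2264
- Effect size = 0.10/0.2264 = 0.4417, as stated
- Two-sided t test, alpha 0.05, power 0.80: 82 per arm, 164 in total, as stated (power 80.3%)
- Reference points: 100 per arm with no loss gives 87% power; 80 per arm (200 less 20%) gives 79.3%

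**2. Expected difference under LOCF.** Let p be the share lost in an arm and f the share of the final mean response reached at the carried-forward session. The arm mean becomes m × (1 − p + p·f), so

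difference = 0.32 × (1 − p₁ + p₁f) − 0.22 × (1 − p₀ + p₀f).

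Example, 25% real / 15% sham, f = 0.5: 0.32 × 0.875 − 0.22 × 0.925 = 0.2800 − 0.2035 = 0.0765.

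The protocol gives neither f nor the split of loss by arm, so both are assumptions shown over a range. Power is for 100 per arm with the SD held at 0.2264.

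| Loss real / sham | f = 0 | f = 0.5 | f = 0.75 | f = 0.9 |
|---|---|---|---|---|
| 20% / 20% | 0.080 (70%) | 0.090 (80%) | 0.095 (84%) | 0.098 (86%) |
| 25% / 15% | 0.053 (38%) | 0.0765 (66%) | 0.088 (78%) | 0.095 (84%) |
| 15% / 25% | 0.107 (91%) | 0.1035 (90%) | 0.102 (89%) | 0.101 (88%) |

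**3. No true effect.** Take both means as 0.22 and SD 0.20, linear build-up, loss completely at random, and dropout uniform over sessions 0 to 11. The mean f is 5.5/12 = 0.458, so the false difference is 0.22 × (p₀ − p₁) × (1 − 0.458).

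- 20% / 20%: zero; simulated rejection about 5%
- 15% / 25%: 0.22 × 0.10 × 0.542 = 0.012; simulated rejection about 7% to 8%
- 10% / 30%: 0.22 × 0.20 × 0.542 = 0.024; simulated rejection about 14% to 15%. A coarser grid of four visits, with SDs 0.25 and 0.20, gave about 11%

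**4. Do the volumes already planned support something better?** In a simulation with four equally spaced visits, linear build-up, 100 per arm and a true difference of 0.10, a likelihood estimate from the same visits was compared with LOCF.

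| Loss real / sham, completely at random | LOCF | Likelihood |
|---|---|---|
| 20% / 20% | 0.090 | 0.100 |
| 30% / 10% | 0.063 | 0.100 |
| 10% / 30% | 0.118 | 0.101 |

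When poor early responders left more often, the likelihood estimate stayed at 0.099 to 0.101, while LOCF ranged from 0.073 to 0.113.

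**5. Participants with no post-baseline volume.** The text of the Primary outcome section describes the denominator of ARLVR as the baseline excess volume. On that reading, carrying baseline forward gives zero change. The printed formula has V_AB − V_AL as denominator, so carrying baseline forward gives 0/0. Small early changes are also unstable as printed. For illustration, take the affected arm from 2400 to 2395 mL and the unaffected arm from 2000 to 1990 mL. The printed formula gives (5 − 10)/5 = −100%, and the text gives (5 − 10)/400 = −1.25%.

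**The case against.** **No time course is stated.** The protocol gives the schedule, the number of sessions and the measurement times, but no trajectory of response. A reader might infer from a 12-session course that the plan expects the effect to accumulate, and that LOCF therefore contradicts the plan. The text does not support that. Build-up is an assumption, and if most of the response comes early the bias is small: at f = 0.9 and balanced loss the difference is 0.098. This objection stands, which is why the size is given as a range.

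**At the planned loss the harm is modest.** With 20% lost in each arm and f = 0.5, power is about 80%, which is the design target and close to the 79.3% of a complete-case analysis of 160. The larger effects need an unequal split that no section gives. This also stands. It limits the size of the concern but does not remove it, because the split is unknown in advance and the ITT rule is fixed now.

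**The estimate and its standard error need not both be wrong.** A reader might conclude that they must be. With balanced, completely random loss and no true effect, LOCF leaves the difference unbiased and the rejection rate at about 5%. The calculation in step 2 holds the SD fixed, so it shows no distortion of the standard error.

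**The carried value is not necessarily early.** A withdrawal evaluation is foreseen where feasible, so it may be a value from the day of leaving. That still precedes week 4 and does not cure LOCF. The PP analysis is no substitute, since it selects participants by compliance.

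**A mixed model has its own assumption.** It is valid when dropout depends on observed data, and it estimates the outcome as if participants had continued. This is correct and has to be written into the plan.

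**Conclusion.** The point holds in a limited form. The protocol fixes LOCF as its only ITT missing-data rule for a last-session endpoint, while repeated volumes of both arms that would support a less assumption-laden analysis are set aside for monitoring.

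If response builds over the sessions, the planned difference of 0.10 would be estimated on average as follows, against 87% power with no loss:

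- 20% / 20%: 0.080 to 0.098, power 70% to 86%
- 25% real / 15% sham: 0.053 to 0.095, power 38% to 84%
- 15% real / 25% sham: 0.107 to 0.101, power 91% to 88%

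With no true effect, harm arises only when loss is unbalanced or related to outcome.

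That LOCF is a weak choice here is well supported. The exact size is not: it rests on an assumed time course, assumed dropout timing, assumed splits by arm and a fixed SD. No single direction of bias can be claimed.

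**What to change.** 1. Reconcile the printed ARLVR denominator with the text of the Primary outcome section first. Until then neither LOCF nor any model of the outcome is well defined.
2. Make the primary ITT analysis a mixed model for repeated measures on the session volumes already collected, expressed as proportional reduction in baseline excess volume. Include arm, visit, arm-by-visit, centre and baseline excess volume, and take the arm contrast at session 12. Multiple imputation by arm is an acceptable alternative.
3. Amend the abstract's statement that only baseline and last-session data enter the outcomes.
4. State the missing-at-random assumption and add a delta-adjusted or reference-based sensitivity analysis. Keep LOCF at most as a further sensitivity analysis.

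The cost is revised analysis wording, a slightly more complex model and some programming, with no new visits. Participants with no post-baseline volume add little to the model, so their number should be reported by arm. Measuring withdrawn participants at week 4 would address the ITT question more directly, but it would be additional data collection and the change above does not depend on it.

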## Discussion

BCRL can impose great burden on the society and cause significant physical and psychological morbidity to patients [42]. Despite the wide application of less invasive surgical techniques, risk for the development of BCRL still remains [43]. Current treatments options for BCRL are either expensive or rather time consuming [44]. Traditional acupuncture emerges as an efficacious, economical, and convenient choice to manage this chronic condition with few side effects, according to several pilot reports [30–35] and our clinical observation. However, after a thorough search in Pubmed and Embase for relevant articles, we found existing studies on this issue were case reports, small single-arm studies [30–33], or parallel studies using regular routine management or Diosmin as a comparison [34, 35], which cannot rule out the placebo effect and needs to be confirmed by rigorously-designed, large-scale studies. The efficacy of real acupuncture over sham acupuncture in dealing BCRL has not been fully illustrated. Therefore, additional research is required to confirm the efficacy and cost-effectiveness of acupuncture on BCRL.In this study, we will adopt Streitberger needle as the sham-acupuncture instrument. Compared with other methods such as placebo points acupuncture, shallow acupuncture at real acupoints and shallow acupuncture at placebo points, Streitberger needle have significant advantages, which make it a perfect choice to keep consistency and credibility, and avoid possible efficacy brought by placebo point acupuncture or shallow acupuncture. This method has been used in several studies with good performance, and was recommended as a reliable sham control [45–47]. Another merit of this study is the measurement instrument we choose. As pointed out above, perometer can easily and swiftly measure the volume of a participants’ limb with high reliability and minimal inter-operator variability compared with other conventional methods, such as volumeters (using a water displacement tank to measure volume) and tape measures (using a tape to measure limb circumference) [48–50], although the measurements from different methods are not interchangeable [51]. According to the data collected from patients and previous reports, the day to day variability in limb volumes is around 0.5 [52]. What is more, to better embody the real effect of acupuncture on BCRL, we use the ARLVR, a more reasonable and practical index that is calculated based on the surplus between the affected arm and the contralateral arm. Theoretically, it can exclude the interfering factors such as base effect and weight fluctuation.

However, there are some limitations in this study. First, to maximally rule out the placebo effect and subjective bias, a standardized acupoint regimen is applied in this trial, which is not in accordance with the concept of individualized therapy of CTM. And additional studies are needed to determine the difference between the standardized acupoint regimen and the individualized acupoint regime. Second, according to TCM, de qi, the needle sensation during acupuncture, is regarded as an important sign of successful acupuncture, and is essential for exerting the clinical efficacy of acupuncture. However, for blinding purpose, acupuncturist are forbidden to enquire about it in both groups in this trial. Finally, as acupuncture is common approach in dealing various symptoms in China, chances are good that some participants in the sham-acupuncture group may feel the difference. Double blindness is not applied in this study, given that the procedure is conducted by the acupuncturists.

In conclusion, this article presents a rigorously designed trial to verify the efficacy of acupuncture on BCRL. The results of this trial will provide more information on this issue.

## Abbreviations

ARLVR: Absolute reduced limb volume ratio
BCRL: Breast cancer related lymphedema
CI: Confidential interval
DSMB: Data and Safety Monitoring Board
ECG: Electrocardiograph
ES: effect size
GPH: Global Physical Health; GMH: Global Mental Health.
IAE: Incidence of adverse events
ITT: Intent-to-treat
PP: per-protocol
PROMIS: Patient-Reported Outcomes Measurement Information System
SD: Standard deviation
TCC: Trial coordinating committee
TCM: Traditional Chinese medicine
TSC: Trial steering committee
